#### Other data

Other variables collected in participant questionnaires are age, gender, marital status, co-morbidities, pain location using a pain manikin, duration of the knee problem, experience of exercise and work status.

The following process data will also be recorded from the physiotherapy case report forms: number of treatment sessions attended, the main content of each treatment, physiotherapists contact time with participants, the number of treatment withdrawals and treatment non-attendances (DNAs).

### Sample size

The sample size for the main trial will be based on the primary outcome measures: WOMAC pain and function subscales
[48] and will compare 6 months post-randomisation outcome for the usual care group with either of the two other intervention groups. We chose 6 months since our TOPIK trial
[15] showed the effects of exercise had reduced by this point with usual physiotherapy care. The BEEP trial is powered to detect an effect size of 0.35 for both WOMAC pain and function; an effect size classified as ‘small’ to ‘moderate’ using standard benchmarks by Cohen
[61]. We chose to power the trial based on a specified effect size (rather than minimum important change) as Terwee et al 2009
[62] report a lack of consensus as to minimum important change on the WOMAC. From our previous trials
[19], we estimate that the standard deviation for WOMAC pain and WOMAC function at 6 months follow-up will be 5 and 17 respectively. An effect size of 0.35 therefore equates to a 1.75 point difference on WOMAC pain and a 5.95 point difference on WOMAC function. To achieve 80% power and a 5% significance level (two tailed) we require 129 patients per treatment group, giving a total sample of 387 patients
[63]. Allowing for a 20% loss to follow-up rate (informed by our previous knee pain trials
[15,19]) we aim to randomise a total of 500 participants to the trial over a period of 18 months.

For practical reasons, the sample size will not be inflated to allow for clustering of individual patients being treated by the same physiotherapist
[64,65], but rather the trial will provide useful estimates of clustering effects and we will adjust for therapists in a sensitivity analysis. It is anticipated that a minimum of 36 physiotherapists (12 per treatment group) will be trained to deliver the trial treatments and that each physiotherapist will treat approximately 18 patients. Thus at the end of the trial, we will be able to estimate an intra-class correlation (ICC) to inform future similar trials.

A formal power calculation was not completed to determine the number of patients to wear an accelerometer. The sample size of 30 per group is based on practical considerations (restricted by the number of accelerometers available for data collection) and on having a reasonable sample size to analyse the data using parametric statistics.

### Embedded qualitative interviews

Qualitative methods have an important role to play in evaluating complex interventions
[66] and in helping to interpret the findings from RCTs
[67,68]. In the BEEP trial embedded, longitudinal, qualitative interviews will explore participants’ experiences of treatment, their views of the acceptability of each intervention, the impact of the interventions on participants' exercise and general physical activity behaviour and the explanations for change in knee symptoms and exercise behaviour over time. Topic guides will include questions that explore participants’ views of their physiotherapy treatment, how they got on with their exercise programme and what factors they felt helped or hindered them to adhere to the exercises following the end of their treatment contact with the physiotherapist, and approximately 12 to 18 months later. We will also ask what they feel the future holds for their knee problem. Interviews will be semi-structured, face to face and will last up to one hour. Interviews will be longitudinal in that they will be conducted following physiotherapy treatment completion, and also in the longer-term 12 to 18 months later (timed to be after their 18 month BEEP follow-up questionnaire). The number invited will be determined by ongoing data analysis and theme saturation but it is anticipated to continue until approximately 30 sets of longitudinal interviews have been conducted. Purposive sampling based on data collected in the 3 and 6 months follow-up questionnaires will ensure a diverse range of characteristics in terms of demographic details (age and gender), intervention group, severity of knee condition determined by WOMAC pain and function scores (as this could be linked to participants’ willingness to exercise), and changes in WOMAC scores after intervention completion (as these could be linked to participants’ views about success of the BEEP interventions and longer term exercise adherence). With participants’ written consent, interviews will be audio-recorded and transcribed verbatim by professional transcribers. All transcripts will be anonymised and data management and analysis will be facilitated by NVivo (QSR International, Version 9). Earlier interviews (at the end of physiotherapy treatment completion) will be analysed and inform the interview content of the interviews at the longer-term follow-up.

### Statistical analyses

The trial analysis will be conducted and reported using the Consolidated Standards of Reporting Trials (CONSORT) guidelines
[65,69,70].

#### Recruitment and follow-up

The number of participants identified and recruited using each recruitment method will be reported in a flow chart, along with the number of participants returning a questionnaire at each follow-up stage. The flow chart will include reasons for trial ineligibility and withdrawal (when available) and will be used to compare the recruitment success of each method to inform future trial recruitment.

The baseline characteristics of participants will be reported for the three recruitment methods, for the three treatment groups (to explore the effectiveness of randomisation) and for those with and without data at each follow-up time point (to explore any selective loss to follow-up). Any differences between treatment groups will be described by visual inspection rather than statistical testing.

#### Primary and secondary trial analysis for clinical outcomes

The primary and secondary trial analysis will be conducted blind to intervention group by the statistician (EN) and an independent statistician will verify the analysis of the primary outcomes. The primary analysis will compare each of the Individually Tailored Exercise and Targeted Exercise Adherence interventions to usual physiotherapy care on an intention-to-treat basis, for the primary outcome at 6 months post-randomisation. Secondary analysis will include the analysis of the primary outcome at the secondary endpoints (3, 9, 18 and 36 months) and analysis of the secondary clinical effectiveness outcomes, as indicated in Table 
2, at all follow-up time points. Estimates of clinical effect will be derived using analysis of covariance (ANCOVA) for continuous outcome measures and logistic regression for dichotomous outcomes and will be presented as mean or percentage differences (as appropriate) with 95% confidence intervals after adjustment for baseline covariates defined *a priori* as:

• Baseline for the outcome of interest^a^

• Age

• Gender

• Duration of the knee problem

• Physiotherapy treatment centre (as was used in the randomisation algorithm)

A secondary analysis will also be completed to model the longitudinal trajectory of WOMAC pain and function over time (the primary outcome) and the PASE physical activity measure using generalized estimating equations. Model predictors will include the *a priori* covariates listed above (with the baseline for the outcome of interest modelled as a covariate rather than outcome as recommended in Peduzzi et al
[71]), time, treatment and a time*treatment interaction. A linear model will be fitted to the data (with time as a continuous measure) initially, however, if the trajectory over time is non-linear, quadratic or cubic terms will be explored. It will also be explored that conclusions do not differ if time is represented in the model as a categorical variable. All model estimates will be presented with 95% confidence intervals derived using robust standard errors.

The primary and secondary trial analyses will be conducted after imputation of missing data has been completed. Missing data will be imputed using the multiple imputation routines in STATA v11. All primary and secondary clinical effectiveness outcomes (excluding accelerometry) and the a priori covariates will be included in the imputation model and will have their missing data imputed. The intention-to-treat analysis will include participants who are protocol violators, but will not include participants who are post-randomisation exclusions. Information on any adverse events will be reported. We plan to analyse and publish the results of the trial after the 18 month follow-up is complete, and then produce a follow-up paper at 36 months.

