#### Recruitment and consent of participants to the BEEP trial

From identification methods (1), (2) and (3) above, those who meet the eligibility criteria and who agree to further contact will be posted information about the BEEP trial (a cover letter, a participant information sheet (PIS) (See Additional file
1 for a copy of the PIS), a baseline questionnaire, a consent form and a freepost return envelope). No less than 48 hours after receiving the posted information, a PCRN nurse will telephone the person to further check and confirm eligibility. This check will cover the full eligibility criteria in order to ensure that only those who meet these criteria are then recruited to the trial. In addition, the nurse will screen out individuals with known unstable cardiovascular disorders and those who have such severely restricted mobility that they would not be able to get to the physiotherapy clinics for treatment. All potentially eligible participants will have the opportunity to discuss the trial with the research nurse prior to deciding whether or not to participate. Those who wish to take part in the trial will be asked to sign and date the written consent form, supported by the research nurse over the telephone, and return it along with their completed baseline questionnaire to the nurse in a pre-paid envelope. Those who do not wish to take part will be asked to indicate this on the consent form and to return it to the nurse in the pre-paid envelope provided. This consent process was tested in the pilot study and regular audits of the nurse telephone calls will form part of the quality assurance procedures of the BEEP trial. It is possible, based on this consent method, that a very small number of participants in the BEEP trial will be found to be subsequently ineligible since it is only after consent that participants have a detailed physical assessment by a BEEP trial physiotherapist. Examples of this are expected to include a very small number of participants who have radiating leg pain from a spinal problem or a hip joint problem with referred pain in the area of the knee.

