#### Randomisation and allocation concealment

Following receipt of a signed consent form and baseline questionnaire, the BEEP trial administrator will randomise the participant using a computer-generated randomisation schedule provided by the Musculoskeletal Clinical Trials Unit (CTU) at Keele University, password-protected to ensure that research nurses and trial statisticians remain blind to treatment allocation. Participants will be individually randomised to one of the three treatment groups using random permuted blocks of size 3. To ensure that patients at each physiotherapy clinic have a chance of receiving any of the interventions, randomisation will be stratified by physiotherapy clinic. Following randomisation, the trial co-ordinator will liaise with the appropriate physiotherapy clinic to arrange the first appointment for each trial participant. The patient will then be informed in writing of the date, time and location of their first appointment in the physiotherapy clinic. The GP of each trial participant will be sent a letter to confirm that their patient is taking part in the BEEP trial. Thus our procedures ensure baseline data are collected prior to randomisation, that the allocation is concealed until after the patient has been recruited into the trial and until the moment of randomisation and that the person assigning participants to intervention groups (study administrator) has no involvement in the eligibility screen, consent or treatment processes.

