### Sources of bias

Selection bias at recruitment will be avoided by separating the processes of determining patient eligibility and treatment allocation and by using random permuted blocks overseen by the CTU, not allowing physiotherapists assessing and treating patients to predict the next allocation in their clinic. Trial participants will know they are having physiotherapy-led exercise and brief details about the three interventions (see Additional file
1 PIS). It is not possible to blind physiotherapists but they will deliver treatment to participants in only one of the three intervention groups. A PCRN nurse blind to treatment allocation will obtain informed consent and oversee the collection of baseline and follow-up questionnaire data, and will collect minimum data over the telephone where necessary. An evaluation of the success of nurse blinding procedures will be completed and a procedure for reporting incidents where blinding has been compromised will be in place.

Data entry, coding, security, storage and management will follow the standard operating procedures in the CTU at Keele University. Data enterers will receive training in line with CTU procedures and will be blind to the identification of the three intervention groups. Random 10% data entry accuracy checks will be conducted at regular intervals, data accuracy will be audited and accuracy rates recorded. The trial statistician (EN) will remain blind until after the creation of a locked analysis dataset at 18 months follow-up and the completion of the primary and secondary analyses.

Comparing available variables between consenting and non-consenting individuals, trial participant withdrawals and completers will be carried out to evaluate external validity. All participants will be free to withdraw from the trial at any time without having to give any explanation. Where possible, we will collect information about the reasons for withdrawal from the trial. Using validated outcome measures will reduce measurement error. Treatment will be recorded by physiotherapists in standardised formats and audits of these case report forms will be undertaken throughout. Feedback to physiotherapists delivering the interventions will be provided, where necessary, so they can modify and improve the delivery of the interventions. Each intervention is supported by a specific protocol and documentation, developed for the BEEP trial and previously tested in the pilot study.

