### Physiotherapists delivering the interventions

Up to 50 physiotherapists in the participating services will be trained and supported to deliver one of the three BEEP trial interventions. A training programme has been developed and tested in the pilot study and consists of a stepped training course as follows: physiotherapists delivering usual care will attend the first day only, those delivering Individually Tailored Exercise will attend the first day plus a further two days of training (total of three days of training) and those delivering Targeted Exercise Adherence will attend the first three days plus a further two days (total of five days of training). On-going support to adhere to the treatment protocols will be offered through PCRN physiotherapy research facilitators who have also undertaken the BEEP training programme and who will conduct regular audits of physiotherapy case report forms to investigate treatment fidelity. All physiotherapists will be invited to evaluate the training programme through completion of brief questionnaires before and directly following their training and at the end of treatment of all BEEP trial participants (approximately 18 months later). Further workshop refresher sessions to support BEEP physiotherapists will be provided during the course of the trial. The full details of the content and justification for the training programme and the observed changes in physiotherapists’ attitudes, beliefs and intended behaviours through the use of case vignettes will be provided in full in a separate publication.

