#### Cost-effectiveness analysis

The primary economic analysis will be conducted at 18 months, with additional analysis at 36 months. An intention-to-treat analysis will be undertaken. Multiple imputation techniques will be used to deal with missing EQ-5D-3 L scores and resource use data, ensuring that all eligible trial participants are included in the base case economic evaluation. All estimates will be presented as means with 95% confidence intervals.

The base case cost analysis will adopt a NHS and personal social services (PSS) perspective. A broader costing perspective will be considered in a sensitivity analysis, taking into account NHS/PSS costs, patients’ personal expenditure and costs associated with work loss. All costs and outcomes beyond 12 months will be discounted at the standard UK rate of 3.5%.

The estimation of cost-effectiveness within this trial will focus on the principles of dominance and extended dominance. Dominance is a straightforward concept; if an intervention is less effective and more costly than at least one of its comparators, it is not included for further consideration with regard to the estimation of cost-effectiveness. Extended dominance is applied in incremental cost-effectiveness analysis when an intervention is less effective and more costly than a linear combination of two other strategies; the purpose is to remove from consideration those strategies whose costs and benefits are improved by a mixed strategy of two other alternatives. The practical application of cost-effectiveness analysis is to compare an intervention with the next most effective strategy, therefore strategies are ordered in term of QALYs from least to greatest. Failure to remove all dominated or extendedly dominated strategies may lead to comparisons that are not with the next best alternative but with irrelevant alternatives.

The robustness of the results will be explored using sensitivity analysis. Deterministic sensitivity analysis will explore uncertainties in the methods employed to analyse the data, for example a complete case analysis as an alternative to using an imputed data set, any assumptions made in the analysis and the generalisability of the results to other settings.

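### The primary analysis is called intention-to-treat but leaves out post-randomisation exclusions, and the article does not secure that these exclusions are independent of arm

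*Protocol article*

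**What the plan says.** In *Primary and secondary trial analysis for clinical outcomes*, each new intervention is compared with usual care "on an intention-to-treat basis, for the primary outcome at 6 months post-randomisation". The same section then sets the population: "The intention-to-treat analysis will include participants who are protocol violators, but will not include participants who are post-randomisation exclusions". It does not define the excluded group.

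Four other places in the protocol article bear on who that group might be:

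- *Recruitment and consent of participants to the BEEP trial* expects that "a very small number of participants in the BEEP trial will be found to be subsequently ineligible", because "it is only after consent that participants have a detailed physical assessment by a BEEP trial physiotherapist". Its examples are leg pain arising from the spine and hip pain felt at the knee.
- *Randomisation and allocation concealment* fixes the order of events: "Following randomisation, the trial co-ordinator will liaise with the appropriate physiotherapy clinic to arrange the first appointment for each trial participant".
- *Sources of bias* states: "It is not possible to blind physiotherapists but they will deliver treatment to participants in only one of the three intervention groups".
- *Cost-effectiveness analysis* also calls its analysis intention-to-treat, and describes the imputation as "ensuring that all eligible trial participants are included in the base case economic evaluation".

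*Sensitivity analysis for clinical outcomes* lists therapist effects, complete cases, unadjusted models and a per-protocol analysis. None is run on all randomised participants.

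**The concern.** Intention-to-treat protects the comparison because everyone randomised is counted in the arm to which they were allocated. Once some people are removed after allocation, that protection depends on the removals being unrelated to arm. Here the finding that leads to removal appears to come from someone who knows the arm and works only in it. *Sources of bias* relies on keeping eligibility decisions apart from treatment allocation. For participants found ineligible late, that separation no longer holds.

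The rule governs the analysis of both primary outcomes. If the economic wording is read the same way, it governs the base-case economic evaluation too. With no all-randomised analysis listed, a reader of the results could not see from the planned analyses whether the exclusions mattered.

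**Working it through.** **1. The sequence.** Put together, the sections give this order: consent and baseline questionnaire, randomisation, first clinic appointment arranged, physical assessment by a trial physiotherapist. The article says only that the assessment follows consent. That it also follows randomisation comes from the appointment being arranged afterwards. That the assessor is unblinded and arm-specific comes from *Sources of bias*. That late-found ineligibles are the people excluded is an inference, but no other route is described.

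**2. The plan's own sample size.** Inputs from *Sample size*: effect size 0.35, SD 5 (pain) and 17 (function), two-sided 5% level, 80% power, 20% loss.

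- n per arm = 2 × (1.960 + 0.842)² / 0.35² ≈ 128.2, rounded up to 129; total 3 × 129 = 387. This matches the protocol.
- 387 / 0.80 = 483.75, so 484. The protocol randomises 500, which is more than needed and not an error.
- Targets: 0.35 × 5 = 1.75 pain points; 0.35 × 17 = 5.95 function points.

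**3. Is power at stake?** With 500 randomised and 20% loss, 500 × 0.80 / 3 ≈ 133 per arm are analysed, and power is 81.4%. Excluding an assumed 1% or 2% of everyone gives 81.2% or 80.8%. The issue is bias, not sample size.

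**4. Size of the bias.** Let e be the share excluded in an arm and g the outcome gap between excluded and retained participants. The all-randomised mean is (1 − e) × R + e × (R + g) = R + e × g, where R is the retained mean. If g is the same in both arms, dropping the excluded shifts the between-arm difference by (difference in e) × g in absolute size.

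The protocol gives no exclusion rate and no outcome gap, so both are assumptions. An arm holds about 500 / 3 ≈ 167 people, so a difference of 1 to 2 percentage points is about 2 to 3 people.

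| Difference in share excluded (assumed) | Gap in SD (assumed) | Bias in SD | Pain points (× 5) | Function points (× 17) | Share of 0.35 target |
|---|---|---|---|---|---|
| 1 point | 0.5 | 0.005 | 0.025 | 0.09 | 1.4% |
| 1 point | 1.0 | 0.010 | 0.05 | 0.17 | 2.9% |
| 2 points | 0.5 | 0.010 | 0.05 | 0.17 | 2.9% |
| 2 points | 1.0 | 0.020 | 0.10 | 0.34 | 5.7% |

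**5. Effect on type I error.** With 133 per arm the standard error is √(2/133) = 0.123 SD. A bias of 0.005 SD moves the two-sided error from 5.0% to 5.02%; a bias of 0.020 SD moves it to 5.3%.

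**The case against.** The strongest reply is that the article condenses a fuller protocol. Who decides on an exclusion, by what criteria and with what review may be set out there or in the SAP. The named examples would normally predate randomisation, and removing people for such facts need not bias anything if the judgement is independent of arm. The analysing statistician is blind, the flow chart will report reasons for ineligibility where available, and the numbers are expected to be very small. The ANCOVA also adjusts for the baseline score, so only a gap that persists after adjustment would count.

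Much of this stands. It limits the size of the problem, and it means that selection by arm is not shown. It does not remove the stated rule. Further criteria would not turn the population into all those randomised, and a blind statistician does not make the clinical finding blind.

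A reader might go further and infer that detection differs by design: up to 4, 6 to 8, or 8 to 10 sessions, and training in which "physiotherapists delivering usual care will attend the first day only", against three and five days in the other arms. From there it is a short step to say that more poor responders are removed from the new arms, so the result favours them. The documents do not support this:

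- The physical assessment is described for participants generally. If ineligibility comes to light at the first visit, later session counts are largely irrelevant. Later contacts in the adherence arm may also be by telephone.
- Nothing links training days to recognising hip or spinal pain.
- Neither a higher exclusion rate in the new arms nor a worse outcome in those excluded is documented.

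The economic phrase also sits in a sentence about imputing missing data, so reading it as the same exclusion rule is only one possible reading.

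**Conclusion.** The point holds in a limited form, as something that should be fixed. It is certain that the intention-to-treat label and the stated population disagree, and that no all-randomised sensitivity analysis is listed. It is a reasonable inference that the exclusions arise from an unblinded assessment after allocation by a physiotherapist tied to one arm. The article does not secure that they are independent of arm.

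Under the assumptions in the table the bias is at most about 0.10 WOMAC pain points, under 6% of the target, and its direction is unknown. Larger figures would need more exclusions than the protocol's own expectation allows. The case for change therefore does not rest on a large expected bias. The rule gives up the protection of randomisation and gains almost nothing in return.

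**What to change.** Replace the population sentence in *Primary and secondary trial analysis for clinical outcomes* with wording such as: *The intention-to-treat population is all randomised participants, analysed in the arm to which they were allocated, including any later found to be ineligible. Those who withdraw consent contribute the data collected up to withdrawal.* Make sure that later-found ineligibles stay in questionnaire follow-up. The planned multiple imputation can handle outcomes that are still missing.

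Add to *Sensitivity analysis for clinical outcomes* an analysis without later-found ineligibles, with ineligibility judged blind to arm on facts that predate randomisation. Report these exclusions by arm and reason.

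In *Cost-effectiveness analysis*, reword the base-case population so that it is also all randomised participants.

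The cost is three wording changes and follow-up questionnaires for a handful of people. There is slight dilution: if an assumed 2% of participants cannot benefit, a true 1.75-point effect is diluted by 0.02 × 1.75 = 0.035 points. The change should be settled before the analysis is unblinded.
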